### Description of investigational intervention

The principles of cognitive remediation therapy are the same across studies; however, CRT protocols often vary in terms of the tasks used. This trial uses a modified version of an adolescent manual developed by [name] [47]. The CRT tasks included in our manual are delineated in Table 1. CRT sessions occur daily (excluding weekends) for 45–60 min every day while adolescents are in hospital, for up to 8 days. We have set an a priori definition of “treatment completion” as six sessions of CRT. Treatment completion for parent involvement component was set a priori at three sessions of either TTP or FFT. Though the median length of stay in hospital is 10 days, it is possible that adolescents may discharge before completing all sessions of CRT. These adolescents will continue to complete all study procedures (i.e., follow-up) but will not be considered treatment completers for feasibility assessment (what percentage of adolescents complete CRT) or data analysis (secondary goals).

Study interventionists include the PI or a graduate student under the PIs supervision. [name] provided initial training in CRT, and will provide supervision and feedback to the PI throughout the study duration. CRT sessions will be audio-recorded and coded for adherence to the manual. Should a study interventionist deviate from the manual (e.g., do tasks out of order), this will be noted in the data set. The interventionist will be informed and further training provided to ensure adherence.

CRT sessions are administered every weekday while the adolescent is in hospital, are conducted in an individual format, and tasks are delivered in a standard order to ensure consistency. Table 1 lists all tasks in the standardized order in which they are presented each session. Table 1 also notes the session in which the task occurs; most tasks are administered in each session. It is possible that not all tasks will be able to be administered due to time constraints or individual variables (i.e., hand flip if the adolescent has an IV). At the end of the pilot study, we will re-evaluate the tasks and determine if all should be included a final manual.

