#### Treatment at usual

Adolescents in this condition will not receive any experimental intervention. They will have a standard hospital stay with all normal contact with a multidisciplinary team of health professionals: attending physician, psychologist, social worker, and dietician. Medical stabilization for adolescents with AN at CHOP has been described elsewhere [51].

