### Outcomes

The primary aim of the study is to evaluate the feasibility and pilot the procedures for an RCT of CRT with a family component delivered during a hospital stay for medical stabilization. Primary outcomes are as follows:Recruitment rates (% of patients admitted who are eligible, % enrolled). Ideally, we will be able to recruit 30% of those eligible and at least four adolescents and their parents a month.Completion rates (% of those enrolled who complete at least 6 sessions). Completion rates will vary based on the medically dictated hospital stay. As we have no control over when an adolescent will be discharged, completion rates will be combined with enrollment rates to determine how many participants would need to be enrolled in a future study (over-enrollment) to ensure the appropriate number of treatment completers.Refusal rates and reasons whyRetention rate (% of those enrolled who completed all assessment points, rate of drop out over 6 months of follow-up). Ideally, we would have a dropout rate < 25%. As adolescents are discharging to various levels of care, we track dropout rates and determine if we have higher rates associated with certain levels of care (e.g., residential treatment).Average length of time to complete measures

We will also pilot procedures and evaluate the following:Ease of record forms (can the study staff use forms effectively and can the interventionist easily record data needed from each CRT session)CRT task adaptations (e.g., are some tasks more difficult for adolescents, are there modifications that need to be made)Staffing needs (are there enough staff to recruit/enroll/assess/and administer CRT?)Acceptably of RCT to medical staff (evaluated through meetings with and feedback from staff (e.g., physicians, nurses, behavioral health)

In addition to piloting the study and assessing feasibility, our secondary goals are to examine relevant outcomes for a fully powered trial. We will examine the following:Willingness of adolescent to engage in treatment post-dischargeAdolescent rate of weight gain post-discharge to 6 monthsParental accommodation in symptoms post-discharge (group differences and over time changes)Changes in set-shifting or central coherence

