#### Power analysis

As this is a pilot study, the primary outcome is understanding the feasibility of implementing a large-scale trial. For the mixed MANOVA and using G*power 3.1.7 [64, 65] with three groups (*n* = 20 per group) and five repeated measures, using a 10% probability of a type I error (α = .10), and a medium effect (*f* = .25), the power achieved was .55.

To assess power in the LGCM, we conducted a series of Monte Carlo simulations with 1000 replications, to determine sample size for sufficient power to evaluate developmental trajectories of our primary and secondary outcome variables in a sample of 60 participants with AN. We used M*plus* 7.2 software for all simulations [66]. Population parameter estimates were derived using data from our prior longitudinal analyses. We concluded sufficient power only if the simulation resulted in parameter and standard error bias less than 10% and 15%, respectively, coverage close to 95% (i.e., confidence interval includes the population value), and power above .80 for the significant effects [66–68]. Power calculations were based on ability to detect small but meaningful effect sizes for intercept (baseline level) and trend (rate of change) factors [69]. The results supported low bias (< 10%), acceptable parameter coverage values for the intercept (.95) and trend (.944) factors, and sufficient power (>.95).

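### The primary completion rate counts the TAU arm in its denominator, so it cannot exceed about 67% and understates CRT completion by one third

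*Protocol article*

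**What the plan says.** All places are in the protocol article.

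- **Outcomes**, among the primary outcomes: "Completion rates (% of those enrolled who complete at least 6 sessions". The same item says that "completion rates will be combined with enrollment rates to determine how many participants would need to be enrolled in a future study", the purpose being "to ensure the appropriate number of treatment completers".
- **Description of investigational intervention**: "We have set an a priori definition of “treatment completion” as six sessions of CRT". Adolescents discharged before that point "will not be considered treatment completers for feasibility assessment (what percentage of adolescents complete CRT").
- **Treatment at usual**: "Adolescents in this condition will not receive any experimental intervention". The Study design section gives CRT sessions only to those randomised to a CRT condition.
- **Participants** and **Power analysis**: anticipated enrolment is 60, with "three groups (*n* = 20 per group").
- **Discussion**: the percentage of treatment completers is to help project how long a full trial would take to recruit. Three years or more at one site is the point at which scaling up, or moving to several sites, would be reconsidered.

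No expected completion rate, completion benchmark, future design or over-enrolment formula is given.

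**The concern.** The numerator can come only from the two CRT arms, while the denominator as written is everyone enrolled. One third of that denominator has no sessions to complete. The retention outcome in the same list also uses those enrolled, and there it is right, because every arm is assessed. For completion it is not.

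The primary aim is whether CRT with a family component can be delivered during a medical admission, and completion is the most direct measure of that. Followed literally, perfect delivery would be published as about 67%. A reader with no benchmark to compare against would take the figure at face value. The rate is also to be carried into planning, where a figure that contains this trial's allocation ratio transfers safely only to a trial with the same ratio.

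**Working it through.** **Inputs.** Enrolment 60 (Participants). Groups of 20 (Power analysis). Two of three arms receive CRT (Study design; Treatment at usual). Completion means at least six CRT sessions (Description of investigational intervention; Outcomes).

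**The plan's own figures.** 3 × 20 = 60, so group size and total enrolment agree. The stated power of .55 also reproduces at 20 per group. For the multivariate group-by-time test (Pillai), with 4 time contrasts, 8 and 110 degrees of freedom, noncentrality 0.25² × 2 × 60 = 7.5 and α = .10, power is 0.551. The 20/20/20 split is therefore a sound basis for what follows. The plan states no completion figure to reproduce.

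**Ceiling.** (20 + 20)/60 = 66.7%. With those randomised to CRT as denominator it is 40/40 = 100%.

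**Recorded rate.** If c is the completion rate among those randomised to CRT, the written definition gives r = c × 40/60 = 2c/3. The values of c are assumptions, since the article gives none.

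| c (CRT arms) | r (as written) |
|---|---|
| 100% | 66.7% |
| 90% | 60.0% |
| 80% | 53.3% |
| 70% | 46.7% |
| 60% | 40.0% |
| 50% | 33.3% |

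**Carrying r into a future trial.** Let M be the number of CRT completers wanted. For illustration M = 40, c = 80%, r = 53.3%.

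1. *Three arms, 1:1:1, target M.* Using r: M/r = 40/0.533 = 75. Using c: 40/0.80 = 50 in the CRT arms plus 25 TAU = 75. The two agree for every c, because M/(2c/3) = (3/2) × M/c.
2. *Two arms, CRT v TAU, 1:1, target M.* Using r: 75. Using c: 50 + 50 = 100. The ratio is 1.5/2 = 0.75, so 25% too few for every c.
3. *r used to inflate a total N of 60 that includes TAU.* Using r: 60/0.533 = 112.5, so 113. Inflating the same N by c: 60/0.80 = 75. The ratio is 1.5 for every c.

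The first use is correct, the second falls short and the third overshoots. The article does not say which, if any, will apply.

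**The case against.** The strongest reply is that context points to the CRT arms. Completion is defined inside the description of the CRT intervention, and the Outcomes section attributes its variation to length of stay, not to allocation. An analyst would be unlikely to report TAU adolescents as failing sessions they were never offered. This is also a condensed article, and arm and session counts will be recorded, so the arm-level rate can be recovered at any time. Finally, the article sets benchmarks for recruitment and dropout but none for completion, so the 67% ceiling cannot by itself fail a criterion.

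Much of this stands as a limit on severity. It does not remove the point. The article does not leave the denominator open. It states one, and nothing elsewhere narrows it; the alternative wording about the percentage of adolescents who complete CRT does not name a denominator.

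Two stronger readings are tempting and are not supported:

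- *That the over-enrolment figure, and hence projected recruitment time, will be too large.* No formula, future design or target number is given. With 1:1:1 kept and CRT completers as the target, which is how the article words the goal, the written rate gives the right total. Inflating a total that includes TAU is not something the text proposes. Nor is the three-year consideration in the Discussion shown to be affected.
- *That families who consent but leave before randomisation definitely count as non-completers.* Table 4 places consent under enrolment and before randomisation, and baseline may run over several days (Measurement strategy), so this is possible. But the Outcomes section does not define enrolled. For projecting enrolment such losses would be relevant, which is a reason to show them separately.

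**Conclusion.** The definition of this primary outcome should be corrected. As written, the completion rate is capped at about 66.7% and understates completion among those offered CRT by one third, whatever the true rate. This rests on a literal reading of the stated denominator and on the planned 20/20/20 split; block randomisation may leave a slight imbalance, which would move the ceiling a little.

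The consequence for planning is a risk and not a demonstrated error. The whole-trial rate is safe only for a future trial with the same 1:1:1 allocation and a target expressed in CRT completers. Outside that it can err either way: 25% too few in the two-arm example, or 1.5 times too many if it inflates a total that includes TAU, compared with inflating that total by the CRT-arm rate. No data are lost, and no stated criterion is shown to change.

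**What to change.** Reword the outcome: completion is the number of participants with at least six CRT sessions divided by the number randomised to CRT + TTP or CRT + FFT (expected 40), reported overall and for each arm (expected 20 each). Report families who consent but are not randomised as a separate count.

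Add that projections of over-enrolment and recruitment time will apply the CRT-arm rate to the CRT arms only, with the TAU number derived from the future trial's allocation ratio.

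The cost is a sentence or two in the Outcomes section. No new data, assessments or participants are needed.

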### Data management and analysis plan

All study participants will receive a unique code that will be used for the duration of the study. This file linking this code to the participants will be stored in password-protected file in the PI’s research lab. All data will be entered into the database using this number. Upon completion of the study, the file linking the participant number to each participant will be destroyed. All data collected will be double scored and double entered into the database to ensure accuracy. The database will be coded. Once the list linking participant study identification numbers to specific participants is destroyed, the database will become de-identified. The data will be stored on a secure network drive that only the PI and team members have access to.

There will be no interim analysis conducted. Study results will be reported at national conferences and data will be submitted for publication.

We will assess treatment credibility and acceptability, track the number of adolescents who meet study criteria, the number approached for enrollment, the number enrolled, reasons why adolescents chose not to participate, dropout rate, and reasons for dropout (using the criteria set forth by DeJong and colleagues) [56]. These data (along with baseline and demographic characteristics) will be summarized by standard descriptive statistics (e.g. means and standard deviations for continuous variables such as age and percentages for categorical variables such as gender).

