### Participants

Participants are male and female adolescents aged 12–18 who present in hospital for treatment of a restrictive eating disorder and at least one caregiver. Only adolescents who have not had prior multidisciplinary treatment for an eating disorder will be included. Inclusion and exclusion criteria are summarized in Table 3.^1^ The total enrollment is anticipated to be 60 adolescents.

**Table 3 Tab3:** Inclusion and exclusion criteria

Inclusion criteria	Exclusion criteria
• Adolescent is between 12 and 18 years of age and living at home with caregiver(s) • Adolescent meets diagnostic criteria for anorexia nervosa (either restricting or binge/purge subtype), or sub-threshold anorexia nervosa according to the DSM-5 criteria • Parent or primary caregiver is willing to participate in CRT + TTP or CRT + FFT sessions (if randomized to either condition) • Consent of all family members who will be participating in treatment • The adolescent is not currently receiving outpatient treatment for the eating disorder (i.e., their first presentation at CHOP)	• Caregiver or adolescent with a co-morbid diagnosis of psychotic disorder, substance dependence, substance abuse, or bi-polar disorder • Caregiver or adolescent with diagnosis of intellectual disability, developmental delay, or autism spectrum disorder • Adolescent with a diagnosis of feeding or eating concerns not elsewhere classified with primary symptoms of bingeing and purging, bingeing without compensatory behaviors, or spitting food with restricting patterns. • Adolescent with diagnosis of avoidant/restrictive food intake disorder • Adolescent or caregiver with acute suicide risk • Concurrent psychosocial treatment for another condition • Adolescent or parent (who will be participating) not fluent in English

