#### Efficacy analysis

Although this is a pilot study, we do want to explore whether or not there is a difference between groups. In order to determine differences between those who are randomized to TAU, CRT + FFT, or CRT + TTP, we will conduct a mixed multivariate analysis of variance (MANOVA) with five repeated measures (time: baseline, discharge, 4 weeks post-discharge, 3 months post-discharge, and 6 months post-discharge) as a within-subjects factor and treatment as a three-level between subjects’ factor. We will also evaluate the condition (treatment) × time interaction. We have three quantitative dependent variables: adolescent treatment engagement, post-treatment weight gain, and symptom accommodation. For initial analyses, we will focus on change pre- to 4-week post-discharge. Any post hoc comparisons will involve comparing subsequent assessments to baseline—as they will be simple planned comparisons. This will allow us to retain the most amount of power (i.e., to enable us to reject the false null hypothesis) [57]. We will also set alpha at .10, which will also increase power. Given these parameters, enrolling 60 adolescents would give us an N comparable to prior research using CRT [58].

In addition to the prior analyses, we will also assess developmental trajectories for rate of weight gain post-discharge, treatment engagement post-discharge, and symptom accommodation using latent growth curve modeling (LGCM) with one growth curve analysis for each variable. LGCM is a structural equation modeling method that models repeated observed measures (measured variables) on factors (latent variables) representing random effects [59]. In LGCM, a level factor is used to represent baseline and trend factors are used to represent rate of change across time. Latent variables define the form of rate of change across time (e.g., linear, quadratic, cubic). Factor loadings are fixed to define baseline level and trend. For a linear trend, the factor loadings are set so they increase uniformly with each unit increase in time. Given is a preliminary analysis, these results will allow us to better understand how change occurs over time. Instead of relying on probability values which subject us to increased type II error rates given the small sample size (i.e., low power), we will assess confidence intervals around our estimates to provide information regarding margins of error. All confidence intervals will be 90% confidence intervals given the small sample sizes.

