## Discussion

The current study is a pilot and feasibility study that examines the implementation of CRT on a medical unit in a large children’s hospital. The description of this protocol followed SPIRIT guidelines [53, 54]. CRT + TTP is compared to treatment as usual and a CRT + contact control group (CRT + FFT). As this is a pilot and feasibility study, we have specified the outcomes we would use in a larger, randomized clinical trial. We plan to focus on the viability of integrating CRT into clinical care, refine recruitment procedures and estimate recruitment rate for a larger trial, and pilot the feasibility of the assessment strategy. Inpatient hospitalization presents as a unique opportunity for us to examine our primary outcomes of interest and establish the feasibility of this type of intervention in the context of a medical unit. Scaling this study up for a larger trial will be feasible if CRT is able to be delivered with little interruption to clinical care, if study interventions are not perceived as burdensome to staff or families, and if participants are able to be successfully recruited and retained through the follow-up phase. By evaluating our rate of enrollment and follow-up and the % of treatment completers, we should be able to determine how long it would take to enroll enough treatment completers to have a fully powered trial. If it would take 3+ years to recruit enough participants from one site, we would need to consider if it feasible to scale up the study or if a multi-site study is needed. The secondary aims could help to inform this—particularly if we see trends in a positive direction. If there is no trend for a difference between TAU and the experimental groups on secondary outcomes and it would take a two-site study to complete, scaling up of this work may not be feasible.

The study intervention builds upon prior research on the use of CRT as an adjunctive treatment for AN. In particular, this study uses CRT as a pre-treatment intervention. While increases in cognitive flexibility are typically the primary outcome of CRT, we posit that CRT may be particularly useful in increasing willingness to engage in treatment upon discharge from the hospital. In addition to assessing stages of change, we are also examining the rate of weight gain when discharged.

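### The primary feasibility rates are planned without intervals, and the sample size of 60 is never tied to their precision, although these rates feed the scale-up projections

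*Protocol article*

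**What the plan says.** - **Primary outcome.** The Power analysis section opens: "As this is a pilot study, the primary outcome is understanding the feasibility of implementing a large-scale trial". The Outcomes section lists recruitment, completion, refusal and retention rates, and the time needed for the measures.
- **Benchmarks.** For recruitment: "Ideally, we will be able to recruit 30% of those eligible and at least four adolescents and their parents a month". For retention: "Ideally, we would have a dropout rate < 25" per cent. Completion is defined ("Completion rates (% of those enrolled who complete at least 6 sessions") but has no benchmark. It is to be combined with enrolment to work out how far a future trial must over-enrol.
- **Analysis of the feasibility data.** The Data management and analysis plan lists eligibility, approach, enrolment, reasons for refusal, dropout, credibility and acceptability, and continues: "These data (along with baseline and demographic characteristics) will be summarized by standard descriptive statistics". Its examples are means, standard deviations and percentages.
- **Analysis of the secondary outcomes.** The Efficacy analysis section argues that, with a small sample, the growth-curve estimates should be read through confidence intervals, set at 90%.
- **Use of the rates.** The Discussion projects, from enrolment, follow-up and completion, how long a full trial would take: "If it would take 3+ years to recruit enough participants from one site", the team would weigh whether to scale up or add sites.
- **Sample size.** The Participants section states: "The total enrollment is anticipated to be 60 adolescents". The support offered is MANOVA power of .55, a growth-curve simulation with power above .95, and the remark that "enrolling 60 adolescents would give us an N comparable to prior research using CRT".

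**The concern.** The authors recognise that a small sample calls for margins of error, but they apply this only to the exploratory growth curves. The outcomes for which the pilot is run get point summaries. Those summaries are then inputs to two derived quantities, the over-enrolment factor and the time to recruit, and both inherit the sampling error of the rates. Without intervals, a reader cannot tell whether a dropout of 23% or a projected 2.8 years is clearly on the favourable side or compatible with the unfavourable one. The sample-size section does not help, because it does not say how well 60 participants estimate any of these rates.

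**Working it through.** **Inputs from the protocol article:** 60 participants, 20 per arm; dropout benchmark below 25%; at least four enrolled a month and 30% of those eligible; completion means six or more sessions, which is possible only in the two CRT arms (2 × 20 = 40); three-year consideration; 90% interval convention.

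**Assumptions not in the article:** 15 months of enrolment (60 ÷ 4), and completion of 50% or 70% for illustration.

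**1. The plan's own power figure.** Repeated-measures MANOVA interaction (Pillai), 3 groups, 5 measures: df1 = 8, df2 = 110, s = 2, noncentrality 60 × 2 × 0.25² = 7.5, α = .10. The noncentral F gives power 0.551. The stated .55 is reproduced. It concerns group differences and says nothing about the feasibility rates.

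**2. Dropout interval.** Wilson 90%, z = 1.645:

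(p + z²/2n ± z√[p(1−p)/n + z²/4n²]) ÷ (1 + z²/n)

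For 15/60, the centre is 0.261 and the half-width 0.091, so the interval is **17.0% to 35.1%**.

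**3. Dropout benchmark, if read on the point value.** Below 25% of 60 means at most 14. P(X ≤ 14) for X ~ Binomial(60, p):

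| True dropout | Chance of meeting the benchmark |
|---|---|
| 15% | 0.97 |
| 20% | 0.79 |
| 25% | 0.45 |
| 30% | 0.16 |
| 35% | 0.04 |

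A true 20% therefore misses it in 1 − 0.79 = 21% of pilots, and a true 30% meets it in 16%. Rates 10 points away are classified correctly in 96% to 97%.

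**4. Completion and over-enrolment.** The factor is 1 ÷ completion rate.
- 20/40: Wilson 90% 37.4% to 62.6%; factor 1/0.626 = 1.6 to 1/0.374 = 2.7.
- 28/40: 57.1% to 80.3%; factor 1/0.803 = 1.2 to 1/0.571 = 1.8.

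**5. Enrolment rate.** Exact Poisson 90% limits for 60 events are χ²(0.05; 120)/2 = 47.9 and χ²(0.95; 122)/2 = 74.4. Over 15 months that is **3.2 to 5.0 a month**.

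**6. Effect on the three-year projection.** For a fixed number of families, time is proportional to 1 ÷ rate. A projection of 36 months made at four a month would run from 36 × 4/4.96 = 29 months to 36 × 4/3.19 = 45 months from enrolment uncertainty alone. Adding completion uncertainty (simulation at four a month and 70% of 40 completing) gives a 95% range of about 2.2 to 4.2 years around a true 3.0 years. In the same simulation, a true 3.5 years is projected as under three years in 18% of pilots, and a true 2.5 years in 87%.

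**The case against.** - **The rules are soft.** The recruitment and dropout targets are introduced as ideals. Passing three years is a matter for consideration, and interruption to care, burden, and trends on secondary outcomes also count. This stands. The 16% and 21% are error rates of a point-value reading, not of a rule that the article fixes.
- **A reader might infer that the scale-up verdict is close to chance.** The documents do not support that. Near-even odds arise only when the true rate lies on the benchmark, and there they arise for any point-estimate rule at any size: 0.45 at 60, 0.47 at 200, 0.48 at 400. What 60 participants produce is a wide grey zone on either side.
- **A reader might infer that 60 rests only on the efficacy test.** It does not: a growth-curve simulation and similarity to earlier CRT studies are also given. None of the three concerns feasibility, so the gap remains.
- **Intervals may be left to a fuller document.** The descriptive statistics are introduced by examples, so intervals are not excluded, and completion is not in that list. This has some force. But the article does state a method for these data and does specify intervals elsewhere, for the less important outcomes. The point concerns that stated allocation and the stated reasons for 60.
- **Firm interval-based cut-offs would settle little.** Requiring the whole 90% interval to lie on one side of 25% (at most 9/60, or at least 21/60) would leave 78%, 90% and 76% of pilots undetermined at true dropout of 20%, 25% and 30%. This stands, and such cut-offs are not recommended as a requirement.

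**Conclusion.** The point holds as a matter of planned analysis and sample-size rationale. The primary feasibility rates are to be given without stated uncertainty, the secondary growth curves are not, and 60 is never related to the precision of a primary rate. At 60, dropout near the benchmark is known to about ±9 percentage points at 90% confidence. Completion, from about 40 families, is known to about ±12 to 13 points, and monthly enrolment to within 3.2 to 5.0. True dropout 5 points from the benchmark would be misplaced in 16% to 21% of pilots on a point reading; 10 points away, in only 3% to 4%. The dropout figures need only the article's 60 and 25%. The enrolment and projection figures rest on the assumed 15 months, and the completion figures on the illustrative 50% and 70%. The pilot's validity is not in question. What is affected is how firmly its rates can be carried into the next trial.

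**What to change.** 1. In the Data management and analysis plan, add two-sided 90% intervals for every primary rate: Wilson for proportions, including completion, and exact Poisson for monthly enrolment. This extends the authors' own convention.
2. Carry both limits, including the unfavourable one, through the over-enrolment factor and the projected time to recruit, and show the resulting range beside the three-year mark.
3. Read the ideal benchmarks (30%, four a month, dropout below 25%) alongside the interval and not from the percentage alone.
4. In the Power analysis section, state the precision that 60 gives for dropout and enrolment, and that 40 gives for CRT completion. For a size already chosen, this describes what the pilot can deliver; it does not justify the number after the fact.

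No extra participants, visits or data are needed. The cost is a few lines of analysis text and feasibility conclusions that will sometimes be less firm.
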